## Abstract

**Background:**

Antidepressants still have some side effects in treating major depressive disorder (MDD), and acupuncture therapy is a complementary therapy of research interest for MDD. Acupoints are sensitive sites for disease response and stimulation points for acupuncture treatment. Prior studies suggest that the biological specificity of acupoints is altered in physiological and pathological situations. Therefore, we hypothesize that the biological specificity of acupoints is associated with the diagnosis of MDD and that stimulating acupoints with significant biological specificity can achieve a better therapeutic effect than clinical common acupoints. This study aims to investigate the efficacy and safety of intradermal acupuncture (IA) treatment for MDD based on changes in the biological specificity of acupoints.

**Methods:**

The first part of the study will enroll 30 MDD patients and 30 healthy control (HC) participants to assess pain sensitivity and thermal specificity of MDD-related acupoints using a pressure pain threshold gauge (PTG) and infrared thermography (IRT). The potentially superior acupoints for treating MDD will be selected based on the results of PTG and IRT tests and referred to as pressure pain threshold strong response acupoints (PSA) and temperature strong response acupoints (TSA).

The second part of the study will enroll 120 eligible MDD patients randomly assigned to waiting list (WL) group, clinical common acupoint (CCA) group, TSA group, and PSA group in a 1:1:1:1 ratio. The change in the Patient Health Questionnaire-9 Items (PHQ-9), the MOS item short-form health survey (SF-36), pressure pain threshold, temperature of acupoints, and adverse effects will be observed. The outcomes of PHQ-9 and SF-36 measures will be assessed before intervention, at 3 and 6 weeks after intervention, and at a 4-week follow-up. The biological specificity of acupoint measures will be assessed before intervention and at 6 weeks after intervention. All adverse effects will be assessed.

**Discussion:**

This study will evaluate the therapeutic effect and safety of IA for MDD based on changes in the biological specificity of acupoints. It will investigate whether there is a correlation between the biological specificity of MDD-related acupoints and the diagnosis of MDD and whether stimulating strong response acupoints is superior to clinical common acupoints in the treatment of MDD. The study’s results may provide insights into the biological mechanisms of acupuncture and its potential as a complementary therapy for MDD.

**Clinical Trial Registration:**

ClinicalTrials.gov, identifier: NCT05524519.

## Introduction

1.

Major depressive disorder (MDD) is a major public health problem and one of the primary causes of disease burden worldwide because of the high lifetime prevalence, high recurrence, and high disability rate (1–3). Due to the impact of COVID-19, there is a 27.6% increase in MDD patients worldwide in 2020, with female and young adults being the most affected (4). A previous study’s results suggest that people with chronic conditions are more likely to suffer from MDD (5), which causes more stress on the patient’s life.

The antidepressant medication is currently the most common method used to treat MDD. Although this therapy has achieved good clinical efficacy, it still has certain defects, such as delayed onset of action, long treatment period, high cost, and easy relapse when the medication is discontinued (6, 7). Those side effects may reduce adherence in MDD patients. Therefore, it is imperative to optimize the clinical treatment plan for MDD.

Acupuncture, as part of traditional Chinese medical (TCM), has been shown to have advantages for MDD (8, 9). Acupuncture has been recorded to treat emotional disorders since ancient times. Moreover, it was found that intradermal acupuncture (IA) improved the changes in vagal function, blood pressure, and Beck Depression Inventory scores in MDD patients (10). Our research team conducted data mining of clinical literature on acupuncture for MDD and found that the current acupoints for MDD treatment cover 14 meridian points and extraordinary acupoints, and the most commonly used points include GV20 (Baihui), LR3 (Taichong), PC6 (Neiguan), SP6 (Sanyinjiao), GV29 (Yintang), HT7 (Shenmen), ST36 (Zusanli), etc (11). Data mining results suggest that there were noticeable discrepancies in the selection of acupoints for MDD, and there is a lack of modern scientific evidence. Therefore, this study will select acupoints by objective detection of biological specificity of acupoints and evaluate the clinical efficacy of IA on MDD in a rigorous and standardized manner.

In the area of acupoint biological specificity research, one study found that the temperature of specific acupoints such as Shenshu (BL23), Mingmen (GV4), and Baihui (GV20) was significantly lower in patients with kidney-yang deficiency MDD than in healthy individuals (12). A meta-analysis found that for high-intensity noxious stimuli, the depressed and healthy groups had similar overall pain tolerance, whereas for low-intensity stimuli, the depressed group had higher sensory thresholds and pain thresholds, suggesting that depression attenuated pain perception (13). The aforementioned studies suggest that the biological specificity of the body surface can change in MDD patients. Furthermore, a review of functional magnetic resonance imaging (fMRI) studies on acupoint specificity concluded that acupoint specificity exists, but 73.4% of these studies were conducted based on healthy subjects, 77.2% chose manual acupuncture as an intervention, and 86.1% focused on immediate efficacy (14). However, there are very few studies on the biological specificity of acupoints in patients with MDD, and a more comprehensive study of their relevance to MDD is needed.

Acupoints are specific regions through which Qi of internal organs and meridians is transported to body surface, and internal organ disorders could be reacted from the corresponding acupoints of the meridians. In recent years, more and more researchers have explored acupoints through various modern scientific techniques, such as their morphological structure (15–17), biological specificity (18), and local material basis (19). Some acupoint biological specificities contain physiological and pathological information related to their functions, and they are the external expression of the body’s vital activities (20). Enhancing research into the biological specificities of acupoints is critical for understanding the substance of meridians and acupoints and disease diagnosis and therapy.

Currently, no studies have been reported on acupuncture for MDD based on changes in the biological specificity of acupoints. Therefore, conducting this study has implications for guiding the clinical treatment of MDD with acupuncture. The well-established detection techniques of pressure pain threshold gauge (PTG) (21, 22) and infrared thermography (IRT) (23, 24) have laid a solid foundation for the correlation study of the biological specificities of acupoints. Therefore, this study will use PTG and IRT to measure pressure pain thresholds (PPT) and temperature at MDD-related acupoints, respectively, to assess 2 biological specificities, namely pain sensitivity specificity, and thermal specificity.

Based on the TCM theory that acupoints are both stimulation points for treatment and response points for disease, we propose the hypothesis that the biological specificity of acupoints is correlated with the diagnosis and treatment of diseases and that stimulating acupoints with significant biological specificity can better treat the disease than clinical common acupoints. In this study, PTG and IRT will be used to objectively present the differences in pain sensitivity specificity and thermal specificity of the MDD-related acupoints in MDD patients and healthy control (HC) participants and to screen the potentially effective acupoints for the treatment of MDD. Then, a clinical prospective randomized controlled trial will be conducted to assess the effectiveness and safety of IA for MDD based on changes in the biological specificity of acupoints.

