### Sample size estimation

2.5.

Since there are no relevant references for detecting the biological characteristics of MDD-related acupoints, we referred to the literature on acupoint detection (23, 27) and planned to recruit 30 MDD patients and 30 HC participants in trial A according to the principle of minimum sample size.

In Trial B, we did not estimate the sample size based on power calculations because there was no reference to indicate how effective the use of IA for MDD might be based on changes in the biological specificity of acupoints. To meet the need for minimum sample size, we instead recruited 120 participants.

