### Biological specificity detection of acupoints (Trial A)

2.11.

To minimize the interference effects caused by confounding circumstances, all examinations will be performed almost simultaneously in the morning. A controlled condition experimental room will be adopted, with a temperature of (26 ± 1)°C, relative humidity of 40–50%, no direct sunlight and abnormal radiant source, no significant air convection, and good sound insulation. All subjects will be prohibited from drinking coffee, tea, alcohol, smoking cigarettes, or eating spicy foods on the examination day. Food and exercise will be also not allowed for at least 1 hour before the trial. After entering the experimental room, subjects will be needed to expose the test site and relax for 30 min before the formal examination to adjust to the surrounding. Throughout the exam, subjects will be asked to remain silent, breathe naturally, and relax. Before the examination, basic physiological parameters including heart rate, blood pressure, and body temperature will be taken from the subject. Based on the results of our group’s data mining of the literature related to acupuncture for MDD, 39 acupoints closely related to MDD will be selected as test sites. The IRT test will be not done on the acupoints where the hair is dense. According to the National Standard for the Name and Positioning of Acupuncture Points (GB/T 12346–2006). The anatomical locations of the acupoints are displayed in Table 3 and Figure 2.

**Table 3 tab3:** Location and indication of MDD-related acupoints.

Acupoints	Location
Head, face, and neck	
Baihui (GV20)	On the head, 5.0 cun directly above the midpoint of the anterior hairline. Or, at the midpoint of the line connecting the apexes of the two auricles.
Yintang (GV29)	At the forehead, at the midpoint between the two medial ends of the eyebrow.
Sishencong (EX-HN1)	At the vertex of the head, a group of four points, 1.0 cun, respectively, anterior, posterior and lateral to Baihui (GV 20).
Shenting (GV24)	On the head, 0.5 cun directly above the midpoint of the anterior hairline.
Shuigou (GV26)	On the face, at the junction of the superior 1/3 and middle 1/3 of the philtrum.
Taiyang (EX-HN5)	In the region of the temples, in the depression about one finger-breadth posterior to the midpoint between the lateral end of the eyebrow and the outer canthus.

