#### PTG

2.11.1.

The FDX25 handheld pressure pain gauge will be used to detect the PPT of acupoints. The probe will be positioned vertically on the measurement acupoint, pressure will be applied slowly and steadily, and pressure will be withdrawn as soon as the patient feels pain. The PPT of the acupoint will be displayed on the gauge. Repeat the procedure 3 times at 5 min intervals.

The data will be entered into Excel. The basic PPT of the acupoint will be determined as the average of the 3 times PPT values. The top 4 acupoints most associated with MDD in PTG test will be selected as PSA by logistic regression analysis.

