#### IRT

2.11.2.

An infrared thermography camera (NEC InfRec R450, Avio Infrared Technologies Co., Ltd., Tokyo) with measuring wavelengths of 8–14 um, a temperature resolution of 0.025°C, and a resolution of 640 × 480 pixels, will be used to record thermal images to assess the heat radiation properties of the acupuncture points. By adjusting the height and angle of the machine, the subject’s measured sites will be on the camera screen distinctly. One researcher will use a cotton swab to mark the tested acupoints, and another researcher will operate the electronic cursor of the camera to the corresponding acupoint localization and record the coordinates. Turn off the lights and focus on the camera, then start recording the thermal images. Using the interval shooting mode, 1 thermal image will be taken automatically every 10s, and 1 min continuously, a total of 6 thermal images will be taken. The subject will be instructed to remain still during the measurement.

The InfRec Analyzer NS9500 (Avio Infrared Technologies Co., Ltd., Tokyo) will analyze all thermal images, displaying different temperatures in different colors and selecting the region where the temperature will be measured. The temperature data collecting parameter of the region of interest (ROI) will be set up as a circular area within a radius of 5 mm from the acupoint, which will be the same size as an acupoint in this study. TROI will be used as the average temperature of the ROI in 1 thermal image. The average TROI in the 6 thermal images will be calculated as the temperature of the acupoint (T_acupoint_). The top 4 acupoints most associated with MDD in IRT test will be selected as TSA by logistic regression analysis.

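### Trial A equates acupoint specificity with the raw reading at each point, so it cannot tell a point-specific MDD difference from a general one

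*Protocol article*

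**What the plan says.** The Introduction announces two properties to be assessed, "namely pain sensitivity specificity, and thermal specificity". Section 2.13.1 defines the first as the PPT of acupoints and the second as their temperature.

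- **Sites (2.11):** "39 acupoints closely related to MDD will be selected as test sites". No other site is named.
- **PPT (2.11.1):** "The basic PPT of the acupoint will be determined as the average of the 3 times PPT values". Then: "The top 4 acupoints most associated with MDD in PTG test will be selected as PSA by logistic regression analysis".
- **Temperature (2.11.2):** the mean over six images of the region around the point. Then: "The top 4 acupoints most associated with MDD in IRT test will be selected as TSA by logistic regression analysis".
- **Sample (2.5):** the authors "planned to recruit 30 MDD patients and 30 HC participants in trial A according to the principle of minimum sample size". Section 2.3 matches the groups on age and gender.
- **Also recorded (2.11):** "basic physiological parameters including heart rate, blood pressure, and body temperature will be taken from the subject". The article gives body temperature no role in the analysis.
- **Background (Introduction):** a cited meta-analysis found higher sensory and pain thresholds in depressed people for low-intensity stimuli, "suggesting that depression attenuated pain perception".

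**The concern.** A reading at one acupoint mixes the person's general level with anything particular to that point. Comparing raw readings between patients and controls, point by point, cannot separate the two. If depression raises pain thresholds across the body, most of the 39 points will be associated with MDD, and the leading four will be ordered largely by sampling noise. The definition in section 2.13.1 would still count the result as specificity.

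At stake is one of the study's stated conclusions. The Abstract, the Introduction and the Conclusion all present a correlation between acupoint specificity and the diagnosis of MDD as something the study will examine. The reading of the PSA and TSA arms as points chosen for a strong local response also depends on it.

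**Working it through.** The plan gives no effect size, SD or power for Trial A, so there is no figure of its own to reproduce.

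**Inputs from the article.** 30 per group (2.5), 39 points (2.11), significance at p<0.05 (2.16). Points under dense hair are skipped for thermography, so the temperature count is somewhat below 39; the proportions below still apply.

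**Assumptions.** Normal readings with SD 1; a uniform MDD-control shift d of 0.3 to 0.5 SD; equal within-person correlation between points of 0.5 to 0.7; a two-sided two-sample t-test per point as a stand-in for one-point-at-a-time logistic ranking.

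**Step 1: model.** Reading at point j in person i = person level + d × MDD + δ_j × MDD + error. The raw group difference at point j has expectation d + δ_j. After subtracting the person's mean over all points it is δ_j − mean(δ), and d drops out.

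**Step 2: general shift only (every δ_j = 0).** The chance that one point reaches p<0.05 is about Φ(d√(30/2) − 1.96).

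- d = 0.3: Φ(1.162 − 1.96) = 0.212; 39 × 0.212 = 8.3 points.
- d = 0.5: Φ(1.936 − 1.96) = 0.491; 39 × 0.491 = 19.1 points.
- Within-person values, any d: 39 × 0.05 = 1.95 points.

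**Step 3: simulation (3,000 to 4,000 studies per setting).**

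| General shift | Raw points with p<0.05 | Centred points with p<0.05 | Studies in which all four leading raw points have p<0.05 |
|---|---|---|---|
| 0 | about 2 | about 2 | 15–17% |
| 0.3 SD | about 8 | about 2 | 48–59% |
| 0.5 SD | 18–19 | about 2 | 79–89% |

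**Step 4: what centring costs.** Let four points carry an extra 0.5 SD in the same direction as a 0.5 SD general shift. The raw top four then contains 3.0 to 3.5 of them and the centred top four 2.5 to 3.2.

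**Step 5: where centring alone misleads.** Of the 39 points, 24 lie on the limbs (11 upper, 13 lower). If only those shift by 0.5 SD, the person's mean moves by 24/39 × 0.5 = 0.31 SD, and the other 15 points appear shifted by −0.31 SD after centring. In simulation about 5.8 to 8.8 of these 15 unaffected points then reach p<0.05, against 0.7 to 0.8 on raw values.

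**Step 6: a joint model is no rescue.** A logistic model with all 39 points and 60 people separated the groups completely in 99% of 200 pure-noise runs, so it cannot serve as an implicit adjustment for the person's general level.

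**The case against.** **It belongs to the analysis plan.** Centring and covariates are commonly left there, and section 2.16 says only that logistic regression will screen points. That holds for the details of the model. It does not hold for the definition of the outcome and the ranking variable, which the article fixes.

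**It is a dispute over a label.** Section 2.13.1 defines the terms operationally, and the rule asks only for the points most associated with MDD. This answers any complaint about the selection rule. It does not answer the conclusion drawn about specificity and diagnosis.

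**Centring can create false specificity.** This stands: Step 5 shows it for a regional shift. It rules out centring as a replacement, but not as a companion that also requires the raw association.

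A reader might also infer more than the documents support:

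- *That the cited meta-analysis shows a body-wide threshold shift.* In the Introduction, the word overall describes pain tolerance that was similar between groups. The higher thresholds concern low-intensity stimuli, and nothing is said about body sites.
- *That a general temperature shift is documented.* The Introduction cites lower temperature at particular points in one MDD subtype, and no general shift.
- *That raw ranking picks the wrong points.* It almost never selects four points whose 0.5 SD local effect opposes a 0.5 SD general shift (0.1 to 0.3 of 4). But those effects cancel exactly, so such points show no MDD-control difference, and a rule seeking association with MDD rightly passes over them.
- *That Trial B is undermined.* Selection is by rank and not by p<0.05, and the randomised comparisons remain valid comparisons of point sets.

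**Conclusion.** The point holds as a limit on what Trial A can conclude. As defined, its outcomes cannot distinguish a local from a general MDD-control difference. Under an assumed uniform shift of 0.3 to 0.5 SD with no local effect, about 8 to 19 of 39 points would look associated with MDD on raw values, against about 2 on within-person values.

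The shift sizes, correlations and uniformity are assumptions, because the documents give none. A general difference is plausible for PPT from the article's own background, and only possible for temperature. The finding bears on the specificity claim; it does not call for changing the selected points or the Trial B arms.

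**What to change.** Keep the raw top-4 selection and the four points per arm fixed in section 2.1. Add a prespecified companion analysis for Trial A:

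1. Report the overall MDD-control shift in PPT and in temperature, each with a confidence interval.
2. Test the group-by-acupoint interaction, or analyse each point minus the person's mean over the tested points.
3. Adjust temperature for the recorded body temperature.
4. Conclude that a point shows acupoint specificity only if it is associated with MDD in the same direction in both the raw and the within-person analysis. Otherwise describe it as associated with MDD.

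The cost is one extra analysis, with no new site, visit or participant. There are four downsides:

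- Fewer points may support a specificity claim.
- Centring is slightly less sensitive when local and general effects agree in direction (Step 4).
- It must not be used alone (Step 5).
- It shows specificity only among the tested points, and says nothing about acupoints against non-acupoints.

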## Materials and methods

2.

### Aim, design and setting of the study

2.1.

The overarching goal of the trial is to evaluate the therapeutic effect and safety of IA for MDD and demonstrate whether stimulating strong response acupoints is superior to clinical common acupoints in the treatment of MDD.

This study will be divided into two parts (Trial A and Trial B).

Trial A will adopt a controlled, assessor-blinded design, in which eligible MDD patients and HC participants will be assessed at acupoints using PTG and IRT. Figure 1A shows a flow chart of the study process. The potentially superior acupoints for the treatment of MDD will be chosen independently based on the outcomes of the PTG and IRT tests. After statistical analysis, four pressure pain threshold strong response acupoints (PSA) and four temperature strong response acupoints (TSA) will be selected, respectively. These two groups of acupoints will be used in corresponding arms in the trial B.

**Figure 1 fig1:**
[figure not shown]
Flow chart of the study process. **(A)** Flow chart of the study process of Trial A. MDD, major depressive disorder. **(B)** Flow chart of the study process of Trial B. PTG, pressure pain threshold gauge; IRT, infrared thermography; PPT, pressure pain thresholds; T_acupoint_, temperature of the acupoint; WL, waiting list; CCA, clinical common acupoints; PSA, pressure pain threshold strong response acupoints; TSA, temperature strong response acupoints; PHQ-9, the Patient Health Questionaire-9 Items; SF-36, the MOS item short form health survey.

Trial B will be a prospective, multicenter, randomized, controlled, patient-assessor-blinded study. Eligible MDD patients will be allocated randomly to waiting list (WL) group, clinical common acupoint (CCA) group, TSA group, and PSA group in a 1:1:1:1 ratio. Figure 1B shows a flow chart of the study process, and Table 1 shows the trial schedule of enrolment, treatments, and assessments. Patients will receive 6 weeks of treatment and all patients will receive basic treatment, IA for CCA, PSA and TSA, respectively. The protocol adheres to the Standards for Reporting Interventions in Clinical Trials of Acupuncture (STRICTA) (25) (Additional file 1) and the Standard Protocol Items: Recommendations for Interventional Trials (SPIRIT) statement (26) (Additional file 2). This study is prospectively registered on ClinicalTrials.gov (NO. NCT05524519).

**Table 1 tab1:** Schedule of enrolment, treatments, and assessments.

	Study period					
	Enrolment	Allocation	Baseline	Treatment period		Follow-up period
**Timepoint**	**−t** _ **1** _	**0**	**t** _ **1** _ **(week 0)**	**t** _ **2** _ **(week 3)**	**t** _ **3** _ **(week 6)**	**t** _ **4** _ **(week 10)**

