**Treatment**						
**Assessments**						
PHQ-9						X
SF-36						X
Pain sensitivity specificity of acupoints			X		X	
Thermal specificity of acupoints			X		X	
Safety assessment						

PHQ-9, the Patient Health Questionaire-9 Items; SF-36, the MOS item short form health survey.

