MDD group	(1) Patients should meet the diagnostic criteria of the ICD-10 diagnostic criteria for MDD; (2) 18 ≤ age ≤ 60, male or female; (3) Participants have clear consciousness and could communicate with others normally; (4) Participants could understand the full study protocol and have high adherence. Written informed consent is signed by themselves.	(1) Participants with serious primary diseases of cardiovascular, respiratory, digestive, urinary, hematological, endocrine, neurological disease, and other serious primary diseases, and the disease cannot be effectively controlled clinically; (2) MDD caused by organic mental disorders, schizophrenia, bipolar disorder, psychoactive substances, and non-addictive substances; (3) Participants with suicidal tendencies; (4) Pregnant or lactating participants; (5) Participants with intellectual disabilities who cannot cooperate with the questionnaire survey; (6) Participants with bleeding tendency, skin disease, allergic constitution, and allergic to adhesive tape; (7) The skin at the test site of participants has scars, hyperpigmentation, red and swollen. IRT is not be performed on female subjects during their menstrual and ovulatory periods; (8) Participants are participating in other trials.

HC, Healthy control; MDD: Major depressive disorder; ICD-10, International Classification of Diseases 10th Edition.

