### Randomization and allocation

2.9.

Trial A is a controlled observational trial without randomization and allocation.

Trial B will use a computerized central randomization system to randomize the participants in the dynamic stratified block, which is undertaken by Zhejiang Taimei Medical Technology Co. Each center will have an independent researcher log into the computerized central randomization system and generate a randomized sequence that divides eligible participants into 4 groups (WL group, CCA group, TSA group, and PSA group) in a 1:1:1:1 ratio. The researcher will have no contact with participants, acupuncturists, outcome assessors, and data statisticians. The allocation results will be stored in the central computerized randomization system password-protected.

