#### WL group

2.12.1.

Patients in this group will not receive IA treatment during the study period. When the study is over, they will receive 6 weeks of the same IA treatment as in the CCA group.

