#### Trial B

2.13.2.

(1) Primary outcome measures: change in the PHQ-9. The PHQ-9 scale is widely used in clinics to assess MDD symptoms and evaluate therapy response (28, 29). There are nine questions on the PHQ-9 scale, each with a score of 0–3 (none: 0; a few days: 1; more than half of the time: 2; almost every day: 3), for a total score of 0–27. PHQ-9 has been demonstrated to be reliable in studies because of its high sensitivity and specificity (30). The accuracy and ability of the PHQ-9 to detect depression results over time have been proven in studies, and it can be utilized as a valid prognostic indicator (31).

(2) Secondary outcome measures: (1) Change in the SF-36: the MOS 36-item Short Form health survey (SF-36) (32) consists of 36 items that provide a comprehensive assessment of the patient’s physical condition and emotional perception in 8 dimensions: physical function (PF), role physical (RP), body pain (BP), general health (GH), vitality (VT), social function (SF), role emotional (RE), and mental health (MH), (2) Pain sensitivity specificity: the PPT change of acupoints, (3) Thermal specificity: the T_acupoint_ change of acupoints.

The PHQ-9 and SF-36 will be assessed before intervention, at 3, 6 weeks after intervention and at the end of 4-week follow-up; biological specificities of acupoints will be assessed before intervention, at 6 weeks after treatment.

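### Table 1 schedules baseline after allocation; if the arm is known by then, patient-reported baselines can shift and bias the three waiting-list contrasts

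*Protocol article*

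**What the plan says.** Table 1 (section 2.1) has the column order "Enrolment Allocation Baseline Treatment period". Enrolment is timepoint −t1, allocation is 0 and baseline is t1 (week 0). Eligibility, consent, demographic and case data are ticked under Enrolment, and allocation has its own column. The acupoint rows read "Pain sensitivity specificity of acupoints X X" and "Thermal specificity of acupoints X X", with the ticks under Baseline and week 6.

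Section 2.13.2 makes change in PHQ-9 the primary outcome. On timing it states "The PHQ-9 and SF-36 will be assessed before intervention, at 3, 6 weeks after intervention and at the end of 4-week follow-up" and, for the acupoint measures, "biological specificities of acupoints will be assessed before intervention, at 6 weeks after treatment". Neither statement refers to randomisation.

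Section 2.9 states "Each center will have an independent researcher log into the computerized central randomization system and generate a randomized sequence". It keeps the results under password in the central system, but does not tie an assignment, or its release, to completed baseline data.

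On the WL arm, section 2.12.1 states "Patients in this group will not receive IA treatment during the study period". Section 2.10 says that patients, evaluators and statisticians are blinded; patients are blinded by separate treatment rooms and by preventing contact between patients.

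**The concern.** A baseline taken after allocation is protected from the effect of allocation only while the patient does not know the arm. Separate rooms can hide which acupoint set is used. They cannot hide whether needles are given at all, so a WL patient knows the arm once told, or once no session is booked.

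PHQ-9 and SF-36 come from the patient's own answers. PPT is read at the moment the patient reports pain. A blinded evaluator does not protect such measures from disappointment or expectation.

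The primary outcome is a change, and section 2.16 analyses it by repeated measures ANOVA over time points before and after the intervention. Baseline is therefore one of the analysed measurements, and a shift in one arm's baseline enters the group-by-time comparison. Section 2.1 names the therapeutic effect of intradermal acupuncture (IA) as an aim. WL is the only arm without IA, so the exposed contrasts are the only ones that compare IA with no IA.

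**Working it through.** The plan gives no power, SD or effect size (section 2.5), so it has no figure to reproduce. The check has two parts.

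**1. Which contrasts and measures are exposed**

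- Four arms give 4 × 3 / 2 = 6 pairwise contrasts.
- Three involve WL (WL–CCA, WL–TSA, WL–PSA). Knowing whether one gets needles or the waiting list can act on these.
- Three do not (CCA–TSA, CCA–PSA, TSA–PSA). All these patients expect needles, so the expected bias by this route is 0 as long as they do not know which acupoint set they have.
- PHQ-9, SF-36 and PPT depend on the patient's report. Acupoint temperature is the mean over six instrument images (section 2.11.2) and is much less exposed.

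**2. Size, if a shift occurs**

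Inputs from the document: 120 patients at 1:1:1:1, so n = 120 / 4 = 30 per arm, and significance at p < 0.05 (taken as two-sided). Assumed, because the document gives none: PHQ-9 SD 4 to 6, baseline-to-follow-up correlation rho 0.3 to 0.7, and a WL baseline shift b of 0.5 to 2 points that is gone by follow-up.

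- Change-score contrast: bias = b, so 0.5 to 2 points.
- Baseline-adjusted contrast: this is the follow-up difference minus slope × the baseline difference, so bias = slope × b. With equal SDs the slope equals rho. At slope 0.5 the bias is 0.25 to 1 point. Over slopes 0.3 to 0.7 it runs from 0.3 × 0.5 = 0.15 to 0.7 × 2 = 1.4 points. Adjustment reduces the bias but does not remove it.

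Rejection rate for one WL-versus-needle change contrast with no true effect (normal approximation, one follow-up time):

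- SE = SD × √(2(1 − rho)) × √(2/30)
- Rate = Φ(b/SE − 1.96) + Φ(−b/SE − 1.96)
- Middle case, SD 5 and rho 0.5: SE = 5 × 1 × 0.258 = 1.29

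| b (points) | SD 5, rho 0.5 | Range over SD 4–6, rho 0.3–0.7 |
|---|---|---|
| 0 | 0.050 | 0.050 |
| 0.5 | 0.067 | 0.059–0.096 |
| 1 | 0.121 | 0.085–0.240 |
| 2 | 0.341 | 0.194–0.705 |

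The direction is not fixed. If disappointment raises the WL baseline score and then fades, WL appears to improve more and a real effect of IA is understated. A shift the other way overstates it.

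**The case against.** The strongest reply is that early disclosure is assumed. No section says when patients learn their arm. The allocation is password-protected, and the researcher who handles it has no contact with participants or assessors. Timepoint 0 and week 0 may be the same visit, and measuring before the intervention is compatible with measuring before randomisation. A condensed article may also leave the release procedure to the full protocol. This stands in part: bias is possible, not shown. But the order is printed in Table 1, so the point concerns what the article states and not merely what it omits.

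A reader might infer more than the documents support:

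- **That every change-from-baseline contrast is biased.** Only the three with WL are exposed. The comparison of strong response with common acupoints, the trial's stated superiority question, is not affected by this route.
- **That Table 1 itself shows PHQ-9 and SF-36 after allocation.** In the text available, those rows carry a mark only at week 10, and the other cells cannot be read. For these two scales the case rests on the only Baseline column following Allocation, together with the wording of section 2.13.2.
- **That WL patients will leave before baseline and have no primary outcome.** No figure supports losses concentrated in WL. WL patients are promised the same IA treatment as the CCA group afterwards, and treatment and assessments are free. A screening PHQ-9 should also exist (section 2.6), although it is not designated as the baseline.
- **That the thermography restriction builds in a delay after allocation.** Table 2 states "IRT is not be performed on female subjects during their menstrual and ovulatory periods" among the exclusion criteria, and eligibility is checked at enrolment. Nothing places the wait between allocation and baseline.

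The size also depends on the shift fading. A shift that persisted unchanged to week 6 would cancel from the change score.

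**Conclusion.** The point holds as a risk to the three WL-versus-IA contrasts. The article schedules allocation before baseline, its timing sentences do not override that order, and blinding cannot cover needles versus no needles. If the arm becomes known before baseline, a transient shift of 0.5 to 2 PHQ-9 points (assumed) biases the change-score contrast by the same amount and a baseline-adjusted contrast by slope × shift. In the middle case, the false-positive rate of one such contrast rises from 0.05 to 0.067, 0.121 and 0.341 for shifts of 0.5, 1 and 2 points. These figures rest on assumed shift, SD and correlation, and illustrate sensitivity; they do not estimate what will happen. Needle-versus-needle contrasts are unaffected by this route, and temperature is much less exposed. The change is worth making because it is nearly free, removes this bias by design, and protects the only contrasts that set IA against no IA.

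**What to change.** - Reorder Table 1: consent and eligibility, then all baseline measures (PHQ-9, SF-36, PPT, temperature), then allocation, then the first session.
- In section 2.13.2, state that the baseline assessments are completed before randomisation, in place of the reference to the intervention.
- In section 2.9, state that the central system releases each assignment only after entry of that patient's baseline data is confirmed.

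The cost is one table, a sentence in each of two sections, and a check in a randomisation system that is already planned. The small downside is that a few patients may complete baseline and then not be randomised.
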